## Abstract

**Background:**

Periodontal surgery has traditionally relied on connective tissue grafts (CTGs) obtained from the tuberosity site to correct gingival recession abnormalities. However, there are challenges to be addressed, including insufficient graft quantity and patient susceptibility. Consequently, titanium-prepared platelet-rich fibrin, or T-PRF, has emerged as a competitive alternative. By combining T-PRF with the modified vestibular incision supraperiosteal tunnel access (M-VISTA) approach, a more conservative way is provided, which may improve the course of treatment.

**Objective:**

The objective of this study is to compare the effectiveness of T-PRF and CTGs from the tuberosity area in managing gingival recession defects using the M-VISTA technique. The study aims to evaluate improvements in clinical outcomes, including pocket probing depth (PPD), clinical attachment level (CAL), relative gingival margin level (RGML), recession depth (RD), and width of keratinized gingiva (WKG), as well as plaque and bleeding indices.

**Methods:**

The proposed methodology entails conducting a randomized clinical trial over 2 years with 24 participants, each presenting with multiple gingival recessions (>2 mm, Miller’s Class I or II) on the buccal or labial aspects of teeth in the maxilla or mandible. Participants will be randomly allocated into 2 groups: the test group and the control group. The M-VISTA technique will be used for root coverage using T-PRF in the test group and tuberosity CTG in the control group as regenerative materials. Their effectiveness will be compared by evaluating PPD, CAL, RGML, RD, and WKG. Additionally, the plaque index will be calculated by dividing the total plaque index score of all teeth by the number of teeth examined, and the papillary bleeding index will be assessed using a periodontal probe with scores evaluated on a scale of 0-4 based on bleeding potential. Data will be analyzed using Student paired and unpaired t tests to compare results from baseline to 3 and 6 months for each group.

**Results:**

Recruitment, participant selection, baseline data collection, and randomization of groups concluded in September 2024, and the intervention phase is scheduled to end in December 2025. The study is expected to be completed by July 2026, with final evaluation, data analysis, and publication preparation taking place between June and July 2026.

**Conclusions:**

Based on existing evidence, we anticipate that the M-VISTA technique with T-PRF will provide superior root coverage compared to tuberosity CTG because no second surgical site is involved. Evidence suggests that T-PRF may offer comparable clinical benefits to CTG, particularly in clinical attachment gain, RD reduction, and gingival thickness, supporting the advancement of minimally invasive periodontal plastic surgery.

**Trial Registration:**

Clinical Trials Registry of India CTRI/2024/07/071619; https://tinyurl.com/ypfe34b5

**International Registered Report Identifier (IRRID):**

DERR1-10.2196/67168

## Introduction

The objective of periodontal treatment is to reestablish the supporting tissues destroyed by periodontitis and anticipate the progression of the disease itself. Aesthetics are another imperative matter that must be considered [1]. Gingival recession (GR) occurs when the apical gingival margin tissue migrates towards the cementoenamel junction (CEJ), leading to the root surface being exposed [2]. Many epidemiological studies have revealed that receding gums is a common condition in day-to-day clinical practice. The frequency of the disease fluctuates between 40% and 100% based on the population and analysis methods [1,2].

Several approaches have been made to manage GR, such as the lateral sliding flap, the double papilla flap, the envelope technique, and graft materials used in conjunction with advanced flap techniques [3]. Recent developments have led to the use of grafting techniques to upgrade the thickness and width of exposed tissue and to cover roots or implant surfaces [4]. The decision to proceed with the procedure is influenced by factors such as recession depth, attached gingiva width, number of teeth, and color balance after surgery. Each technique has its own distinct signs and constraints.

Using the envelope flap method, Raetze in 1985 [5] was the first to use this technique to cover individual GR. As described by Allen in 1994 [6], this method was developed to treat several GRs and later it was described by Zabalegui et al in 1999 [7] as the “tunnel” approach. However, the disadvantage of this technique was entry from a small sulcular point, which increased the possibility of damage and penetration of sulcular tissues, producing unsatisfactory outcomes. Because of these constraints, the vestibular incision supraperiosteal tunnelling access (VISTA) technique was developed by Zadeh [8], as a means of avoiding the potential complications associated with some tunnelling techniques. Several graft materials have been tested with VISTA and proven to be effective.

Modified VISTA (M-VISTA) is a modern and minimally invasive technique used for both generalized and localized GR defects [9]. This technique is particularly useful as it allows easier access to the vestibule by requiring a single vestibular incision that provides entry to the surrounding area. This permits adequate visualization of root and bone structure as well as dehiscence. It facilitates wound repair by reducing the complexity of the tunnelling process [2].

The paradigm for root coverage in periodontal surgery is autologous connective tissue graft (CTG). Traditionally, intraoral donor sites have been found in tuberosity or the palate for soft tissue grafts. Maxillary tuberosity block bone grafting was first described by Tolstunov in 2009 [10]. The evidence that tuberosity has more connective tissue fibers than adipose and glandular tissue and can shrink less is what led to its selection as a donor site [11]. The connective tissue covering the tuberosity contains dense collagen fibers with a well-keratinized epithelial layer. Only CTGs increased buccal gingival thickness after recession coverage, and residual fatty and glandular tissue could potentially impede plasma circulation and revascularization in early healing [12].

However, the thickness or quantity of CTGs may not be adequate for treating multiple GRs or donor area dehiscence in patients with thin palates. Additionally, when a patient refuses surgery twice, CTG is unfavorable [13]. Nonautogenous materials, like acellular dermal matrix and enamel matrix proteins, have applications in treating GR and as a substitute, but they cannot replace gold standards.

Platelet-rich fibrin (PRF) is a concentrated blood product selected for the fixation and revascularization of grafts and flaps because of the growth components it contains. A glass or plastic tube is obscured with activated silica from which a blood sample is extracted, which then generates into a fibrin [14]. Other scientists have conjectured that these particles of silica, which may not be present in the material, act as a catalyst and could potentially harm patients. To overcome the restraints of PRF, titanium-prepared PRF (T-PRF) emerged. Compared to PRF, the fibrin network of T-PRF is more compact as well as bulky. This compact structure of fibrin is important for promoting the retention and recruitment of growth factors into tissue over an extended period [15].

This randomized clinical trial protocol aims to evaluate the effectiveness of T-PRF and CTGs harvested from the tuberosity area using M-VISTA for the management of human GR defects with regards to root coverage (RC), gain in clinical attachment level (CAL), gingival thickness (GT), and improvement in the width of keratinized gingiva (WKG).

## Methods

### Overview

This study is a randomized clinical trial and will be performed over a period of 2 years. After obtaining written informed consent, the study will be carried out on 24 participants who will have multiple GRs (>2mm, teeth presenting Miller class I or II areas) on the buccal or labial regions of teeth in the maxilla or mandible from the outpatient department of Periodontics and Implantology at Sharad Pawar Dental College, Sawangi (Meghe), Wardha, Maharashtra, India. T-PRF clot (test group) and tuberosity CTG (control group) will be the biomaterials used in the M-VISTA procedure for root coverage, and their efficacy will be contrasted.

### Ethical Considerations

The Institutional Ethics Committee Datta Meghe Institute of Higher Education And Research, Sawangi (Meghe), Maharashtra, India, has reviewed and given approval to the study protocol, guaranteeing adherence to moral principles and norms (DMIHER(DU)/IEC/2024/05). This confirmation attests to the fact that participant safety, confidentiality, and informed consent will all be taken into account during the study’s execution.

### Sample Size Calculation

The sample size calculation was based on the formula for determining the required sample size when comparing 2 means, where the outcome of interest is the difference in clinical measurements (such as probing pocket depth [PPD] and CAL) between 2 groups (T-PRF and CTG). The data were evaluated from the earlier research of Collins et al [16] by using the SPSS 27.0 version (IBM Corporation) open-source calculator to determine the sum of squares mean. The outcome of the evaluation was 12. Thus, 12 participants will be unmethodically divided into the 2 groups.

The formula used was:

Where Z_α_ is the Z-value corresponding to the significance level (α), which is typically 0.05 for a 95% confidence level; Z_β_ is the Z-value corresponding to the desired power (β), which is typically 0.20 for 80% power; d_1_ and d_2_ are the SDs of the 2 groups being compared (T-PRF and CTG); and D is the expected difference between the 2 means.

Given Z_α_=1.96 (for a 95% confidence level), Z_β_ =0.84 (for 80% power), SD = (1.32 + 1.10) / 2, and D=1.07 (representing the clinically significant difference between the 2 treatment groups), the sample size calculation is as follows:

[figure not shown]

Thus, the sample size required per group is approximately 12 participants. Since the result is rounded, the final sample size is set to 12 per group.

Randomization ensures that each participant has an equal probability of being assigned to either group, thereby preventing systematic differences between the treatment arms that could influence the outcomes. The random allocation of 12 participants per group was implemented to minimize selection bias and enhance the internal validity of the study using a computer-generated randomization sequence to minimize selection bias and enhance the study’s internal validity.

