#### Clinical parameters

Clinical parameters measured for outcome assessment are relative PPD values, attachment level, relative gingival margin level (RGML), recession depth (RD), WKG, and GT value noted with an UNC-15 probe. An acrylic cast will be made for the patient to obtain clinical parameters. An acrylic stent will be used  to cover the occlusal regions of the test tooth. By directing it using burs, the periodontal probe extends into the deepest defect site. The stent, which will act as a guide for the periodontal probe, will develop longitudinal patterns. Under local anesthesia, the GT will be measured 3 mm below using a rubber stopper and endodontic reamer to assist the gingival edge. From the cementoenamel junction to the gingival margin, RD will be evaluated. WKG will be reached by calculation of sulcus depth and attached gingiva with the UNC-15 probe. These treated areas will be measured clinically on the day of surgery and after 3 and 6 months.

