### Statistical Analysis

Both univariate and multivariate analyses will be performed to evaluate the effect of various variables (such as baseline GT, WKG, and recession length and width) on the final outcomes. Means and SDs will be calculated using standard statistical procedures to ensure significance.

The data will be analyzed as follows:

Changes from baseline to 3 and 6 months will be assessed using a Student paired *t* test.Comparisons between treatment groups at baseline, 3 months, and 6 months will be conducted using a Student unpaired *t* test.

In addition to these tests, multivariate analyses, such as multiple regression and analysis of covariance, will be used to determine the combined effects of covariates like baseline GT, WKG, and recession dimensions on treatment outcomes. These methods will allow for the assessment of potential interactions and the adjustment of confounding variables. The threshold for statistical significance will be set at *P*<.05.

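### No primary outcome or primary time point is designated, the sizing outcome is left open, and 12 to 16 post-treatment comparisons share one unadjusted P<.05 threshold

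*Protocol article*

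**What the plan says.** The Sample Size Calculation states that "the outcome of interest is the difference in clinical measurements (such as probing pocket depth [PPD] and CAL") between the two groups. It then gives "SD = (1.32 + 1.10) / 2, and D=1.07 (representing the clinically significant difference between the 2 treatment groups"), with no outcome, unit or time point attached in the visible text, and concludes that "the final sample size is set to 12 per group".

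The Introduction sets the aim "with regards to root coverage (RC), gain in clinical attachment level (CAL), gingival thickness (GT), and improvement in the width of keratinized gingiva (WKG"). The Abstract's Objective lists probing depth (PPD), attachment level (CAL), relative gingival margin level (RGML), RD and WKG, plus plaque and bleeding indices. The Abstract's Conclusions expect superior root coverage with T-PRF.

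In Methods, "Clinical parameters measured for outcome assessment are relative PPD values, attachment level, relative gingival margin level (RGML), recession depth (RD), WKG, and GT value". The Indices section adds the plaque index and the papillary bleeding index. All eight measures are taken on the day of surgery and at 3 and 6 months.

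Under Statistical Analysis, unpaired t tests compare the groups at baseline, 3 months and 6 months. Regression and analysis of covariance (ANCOVA) are also planned, with covariates that include recession dimensions. "The threshold for statistical significance will be set at" P<.05. No outcome or time is ranked above another.

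**The concern.** A power statement and a 5% error rate mean something only for a named comparison. Here the calculation offers two different variables as examples and one pair of figures for the difference and SD, so the reader cannot tell which hypothesis has the stated 80% power. The analysis then applies the same threshold to every parameter at both post-treatment times. Followed as written, the plan allows any of these comparisons to be presented as the efficacy result of a 24-participant trial whose authors already expect T-PRF to be superior.

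Overlap between measures adds to this. RD runs from the cementoenamel junction to the gingival margin. RGML records the position of the same margin, apparently against the stent. Attachment level combines margin position with probing depth. One shift of the margin, real or by chance, can therefore appear as several significant parameters.

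**Working it through.** **1. The plan's own figure.** Inputs from the Sample Size Calculation: Z values "1.96 (for a 95% confidence level") and "0.84 (for 80% power"), SD = (1.32 + 1.10)/2 = 1.21, D = 1.07. The worked calculation is a figure that is not shown. The standard two-mean formula gives

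n per group = 2 × (1.96 + 0.84)² × 1.21² / 1.07² = 2 × 7.84 × 1.4641 / 1.1449 = 20.05, so 21.

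The stated 12 is not reproduced. That is a separate matter on which this point does not depend. What matters here is that no visible input identifies an outcome or a time.

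**2. The outcome lists side by side.**

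| Place | Outcomes named |
|---|---|
| Abstract, Objective | PPD, CAL, RGML, RD, WKG, plaque and bleeding indices |
| Abstract, Conclusions | root coverage (expected superiority) |
| Introduction, aim | root coverage, CAL, GT, WKG |
| Sample Size Calculation | PPD and CAL, as examples |
| Clinical parameters | PPD, attachment level, RGML, RD, WKG, GT |
| Indices | plaque index, papillary bleeding index |
| Results, expected | PPD, RD, CAL, relative attachment level, RGML, thickness of attached gingiva |

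No row is called primary. Root coverage is in the aim and the headline but not in the list of measured parameters. RD is in that list, and percentage root coverage follows from it as (RD at baseline − RD at 6 months) / RD at baseline.

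**3. The number of post-treatment between-group tests.**

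- Six clinical parameters × 2 times = 12.
- Adding two indices: 8 × 2 = 16.
- The baseline tests (8 more, 24 in all) and the paired within-group tests are left out.

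**4. Chance of at least one false positive when no true difference exists.**

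Under independence, 1 − 0.95^k:

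- k = 12: 1 − 0.95^12 = 0.460
- k = 16: 1 − 0.95^16 = 0.560

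These are upper values, because correlation between tests lowers them. The document gives no correlations, so the following are assumptions: 16 equally correlated normal test statistics, each two-sided at 1.96, simulated with 200,000 draws.

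| Assumed pairwise correlation | At least one false positive among 16 |
|---|---|
| 0.3 | 0.475 |
| 0.5 | 0.375 |
| 0.7 | 0.265 |
| 0.9 | 0.146 |

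**5. The comparator.** One prespecified comparison at one time: 0.05, with no adjustment needed.

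**The case against.** The best defence is that a journal article condenses the protocol, and that multiplicity rules and the labelling of secondary outcomes are usually left to an analysis plan, which is not shown. That is fair for the adjustment method. It does not cover the primary outcome and time, which the sample size needs in order to mean anything and which the article itself leaves open by giving examples. The planned regression and ANCOVA do not settle it either, since they refer to outcomes only in general terms.

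Several stronger readings are tempting and are not supported:

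- **That root coverage is the trial's sole aim and the sizing ignores it.** Root coverage is the headline and the first of four aims, but CAL is also an aim and is one of the two sizing examples. The mismatch is clear for PPD, not for CAL.
- **That the root-coverage question goes unmeasured.** RD is defined and measured at all three times. The gap is that it is not designated primary.
- **That the error rate for root coverage is itself uncontrolled.** A single RD test at 6 months at P<.05 keeps its 5%. What is uncontrolled is the family-wise rate and the choice of which result to headline.
- **That the false-positive risk is 56%.** That is the independence ceiling for 16 tests. Because several measures overlap, the true figure is probably lower.
- **That 16 is the only count.** The Clinical parameters section names six outcome measures, which gives 12 tests. The indices count if the Abstract's Objective is followed.
- **That the difference of 1.07 was never linked to an outcome.** Only the visible prose can be judged. The missing figure may carry a label.

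Some of the differences between lists are also mere condensation. The Methods list contains every clinical parameter in the Abstract's Objective, and leaving GT out of an abstract is minor.

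**Conclusion.** The point holds in this form: no primary outcome or time is designated, the sizing outcome is left open, and 12 to 16 post-treatment comparisons are tested at P<.05 without hierarchy. The family-wise false-positive rate is at most 46% (12 tests) or 56% (16 tests). For 16 tests it is about 38%, 26% or 15% at correlations of 0.5, 0.7 or 0.9. These figures assume no true difference on any measure, and the correlations are assumed. Every scenario shown lies well above the 5% that one prespecified comparison would hold. The achieved power for RD cannot be stated, because the document gives no SD identified as belonging to RD.

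**What to change.** Before analysis (scheduled for June to July 2026), and without sight of outcome data by group:

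1. Designate one primary endpoint that matches the root-coverage aim: RD at 6 months after surgery, compared between groups by the already planned ANCOVA with baseline RD as covariate, at two-sided 5%. Report percentage root coverage descriptively.
2. Label all other parameters and the 3-month comparisons as secondary, with 95% confidence intervals and no confirmatory claim.
3. State which outcome and time the difference of 1.07 and the SDs of 1.32 and 1.10 refer to. If it is not RD, say that the stated 80% power does not apply to the primary endpoint.

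The cost is wording: RD is already collected at both times, and no visit or procedure changes. The downside is that the other parameters lose confirmatory status. The alternative of adjusting across everything is much dearer. Bonferroni over 16 tests sets alpha at 0.05/16 = 0.0031. If the plan's D of 1.07 and SD of 1.21 are assumed for each outcome, that needs 37 per group for 80% power and leaves about 22% power at 12 per group.

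### The stated sample-size inputs give about 20 per group, not 12; 12 per group has about 54% power, not 80%

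*Protocol article*

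**What the plan says.** The Sample Size Calculation section of the protocol article says that the number was derived by comparing two means, T-PRF against CTG. It prints these inputs:

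- significance level: "Given Z_α_=1.96 (for a 95% confidence level"
- power: "Z_β_ =0.84 (for 80% power"
- spread and difference: "SD = (1.32 + 1.10) / 2, and D=1.07 (representing the clinically significant difference between the 2 treatment groups"

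The two SD terms in the formula "are the SDs of the 2 groups being compared (T-PRF and CTG", so each group has its own SD.

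The section then concludes: "Thus, the sample size required per group is approximately 12 participants". It fixes the size at 12 per group. The Abstract and the Methods Overview give 24 participants in total, which agrees. An earlier sentence in the same section does not: "Thus, 12 participants will be unmethodically divided into the 2 groups".

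The Statistical Analysis section compares the groups with an unpaired t test at P<.05.

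**The concern.** The standardised difference implied by the inputs is 1.07 / 1.21 = 0.88. An effect of that size needs about 20 patients per group for 80% power at a two-sided 5% level, so 12 is visibly too few. This is the only justification given for the trial's size, and the 80% power rests on it.

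The error affects how the result will be read. The article expects T-PRF to give superior root coverage and also suggests that it may be comparable to CTG. A non-significant difference from a trial believed to have 80% power would naturally be read as support for comparability. With power near one half, it would support very little.

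**Working it through.** **Inputs, all printed as text in the Sample Size Calculation section**

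- Z for the significance level: 1.96 (two-sided 5%, matching the P<.05 threshold in Statistical Analysis)
- Z for power: 0.84 (80%)
- Group SDs: 1.32 and 1.10, average 1.21
- Difference D: 1.07
- Planned size: 12 per group

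**Step 1. Try to reproduce 12 per group.** For two independent means:

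n per group = (Z_α + Z_β)² × (SD₁² + SD₂²) / D²

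- (1.96 + 0.84)² = 7.84
- 1.32² + 1.10² = 1.7424 + 1.2100 = 2.9524
- 1.07² = 1.1449
- n = 7.84 × 2.9524 / 1.1449 = **20.2**

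With the averaged SD: n = 2 × 7.84 × 1.21² / 1.1449 = 2 × 7.84 × 1.4641 / 1.1449 = **20.05**.

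Either way this rounds up to 21 per group, 42 in total. The stated 12 is not reproduced.

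**Step 2. Look for another route to 12.**

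| Variant | n per group |
|---|---|
| One-sided 5% (Z = 1.645), SD 1.21 | 15.8, so 16 |
| Smaller SD (1.10) in both groups | 16.6 |
| Larger SD (1.32) in both groups | 23.9 |
| Factor 2 left out, SD 1.21: 7.84 × 1.4641 / 1.1449 | 10.03 |
| Same, plus small-sample term 1.96²/2 = 1.92 | 11.95 |
| Variance of one group only: 7.84 × 1.7424 / 1.1449 | 11.93 |

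The last two rows reach 12. Both are one-sample or paired forms that count the variance of only one group, so neither is valid for comparing two independent groups. The worked equation is a figure that is not in the text at hand, so either could be the cause and neither can be confirmed.

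**Step 3. Power of the planned size** (two-sided 5%, D = 1.07, SD = 1.21)

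- Standard error of the difference at 12 per group: 1.21 × √(2/12) = 0.494
- D / SE = 1.07 / 0.494 = 2.166
- Normal approximation: Φ(2.166 − 1.96) = **58%**
- Unpaired t test (noncentral t, 22 degrees of freedom): **54%**

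The t test gives 79.8% power at 21 per group and 81.7% at 22, so 22 is the first size that reaches 80%.

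**Step 4. What 12 per group can detect**

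- Difference detectable with 80% power by the t test: **1.45**
- SD at which 12 per group would give 80% power for 1.07, by the t test: about 0.89, well below both stated SDs
- Expected half-width of the 95% confidence interval: 2.074 × 0.494 = **1.02**, nearly as large as D

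**Step 5. Sensitivity to dropout.** With 11 per group the t-test power is about 51%, and with 10 per group about 46%.

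**The case against.** Four points can be made for the plan.

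1. **The equation is not visible, and the calculation may have been a paired one.** The plan does include paired t tests within groups. A paired t test on 12 patients with SD 1.21 and D 1.07 has 79.6% power, very close to the stated figure. This is a plausible explanation, but it does not justify the number. The section says that the calculation compares T-PRF with CTG, gives an SD for each group, and describes D as the difference between the treatments. A within-group calculation cannot size that comparison.

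2. **Analysis of covariance is also planned and could raise power.** That is true in principle. The sample-size section claims no such gain and gives no correlation from which to compute one. To bring 12 per group up to 80% power, the residual SD would have to fall to about 0.89, so covariates would need to explain 1 − (0.89/1.21)², about 45% of the outcome variance. The 54–58% therefore applies to the unadjusted comparison and should be described that way.

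3. **The Discussion concedes a small sample.** It does so only for generalizability. The 80% power statement is left standing.

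4. **The sentence about dividing 12 participants is only loose wording.** This point stands. The same section gives 12 per group, and 24 in total is stated elsewhere, so the intended size is clear. The sentence needs correcting, but it adds nothing to the loss of power.

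**Conclusion.** The sample-size result is wrong as written. The stated inputs require 20.05 to 20.2 per group by the plan's type of formula (21 after rounding up, or 22 for a full 80% by the t test), against 12 stated. At 12 per group the unadjusted comparison has about 54% power by the planned t test, or 58% by the normal approximation.

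This rests on the printed inputs, a two-sided 5% level, two independent groups of 12 with complete data, and no gain from covariates. It does not depend on the missing equation, because both the inputs and the conclusion are printed as text. The cause of the error cannot be settled from the document. The section gives no unit for D or the SDs and names the outcomes only as examples (probing depth and attachment level), so millimetres would be an assumption.

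**What to change.** In the Sample Size Calculation section:

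- Replace the worked result with the correct one: 20.2, so 21 per group (22 for at least 80% power by the t test).
- State that 24 participants were enrolled and what 12 per group delivers for the unadjusted comparison: about 54% power for a difference of 1.07, 80% power for about 1.45, and an expected 95% confidence interval half-width of about 1.0.
- Name the outcome and unit to which the SDs and D refer.
- Remove or correct the sentence "Thus, 12 participants will be unmethodically divided into the 2 groups".
- If the authors wish to rely on analysis of covariance for power, give the assumed covariate correlation and its source.

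The article reports that recruitment ended in September 2024, so no additional patients are proposed. The cost is a text correction and a less favourable power figure. The final report should interpret the between-group results by their confidence intervals and should not read a non-significant test as evidence that the treatments are comparable.
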